## Abstract

**Background:**

Effective postoperative pain management is essential for optimizing maternal comfort and recovery following cesarean delivery. However, achieving adequate analgesia remains a challenge due to suboptimal pain control and medication-related adverse effects. This study aims to evaluate the efficacy of bilateral quadratus lumborum block using liposomal bupivacaine for post-cesarean analgesia.

**Methods:**

This single-center, open-label, randomized controlled trial will enroll 201 adult parturients undergoing lower segment transverse cesarean section. Participants will be randomized in a 1:1:1 ratio into three groups (*n* = 67 each): Group LB will receive bilateral quadratus lumborum block with liposomal bupivacaine under ultrasound guidance. Group R-P will receive bilateral quadratus lumborum block with ropivacaine in combination with patient-controlled intravenous analgesia. Group P will receive standard patient-controlled intravenous analgesia without regional nerve block. The primary outcome is postoperative pain intensity, assessed using the Visual Analogue Scale during standardized movement at 12, 24, 48, and 72 h postoperatively. A generalized estimating equation model will be used to assess the overall effect of treatment group on pain scores over time. Secondary outcomes include patient-reported Quality of Recovery-15 scores at 24 and 48 h postoperatively; Visual Analogue Scale for pain at rest, measured at 12, 24, 48, and 72 h postoperatively; need for rescue analgesia; postoperative anxiety (assessed by Visual Analogue Scale at 72 h); subjective sleep quality; maximum walking duration; patient satisfaction with analgesia; incidence of nausea and vomiting; postoperative sufentanil consumption and length of hospital stay. Safety outcomes include allergic reactions, wound infection, lightheadedness, headache, circumoral numbness, tongue paresthesia, drowsiness, irritability, blood pressure fluctuations (hypotension, hypertension), respiratory depression (hypoventilation), and cardiac events (bradycardia, tachycardia, arrhythmia, cardiac arrest). Data will be analyzed using a modified intention-to-treat approach.

**Discussion:**

This study aims to provide high-quality evidence on the efficacy of bilateral single-injection quadratus lumborum block with liposomal bupivacaine, compared with standard intravenous analgesia alone and combined with quadratus lumborum block using ropivacaine.

**Ethics and dissemination:**

Ethics approval was obtained from the Ethics Committee of the Affiliated Hospital of Qingdao University (QYFYEC2024-297). All parturients will provide written informed consent. The results of this study will be published in a peer-reviewed journal.

**Clinical trial registration:**

Identifier ChiCTR2500095835.

## Introduction

1

Cesarean section represents one of the most common surgical procedures worldwide (1, 2). It is common for parturients of reproductive age to experience significant anxiety regarding the prospect of postoperative pain following a cesarean section, which often takes precedence over other potential postoperative concerns (3). Effective postoperative analgesia is crucial for optimizing recovery, facilitating early maternal mobilization, reducing hospital length of stay, and promoting breastfeeding initiation (4, 5). Moreover, adequate analgesia not only strengthens maternal–infant bonding but also reduces the risk of postpartum depression, ultimately contributing to the overall well-being and psychological resilience of mothers during the critical postnatal period (6, 7).

In medical practice, clinicians continuously refine postoperative analgesic protocols to enhance both effectiveness and practicality. Patient-controlled analgesia (PCA) pumps have historically been the primary modality for postoperative pain management and remain widely used today, delivering pharmacologic agents via indwelling catheters to epidural, intravenous, and fascial plane compartments (8–10). Although epidural analgesia remains a clinically well-established modality, its implementation frequently elicits patient anxiety and procedural discomfort. Serious complications such as neurological injury and epidural hematoma, along with common adverse events including hypotension, urinary retention, and infection (11). Notably, evidence associates epidural techniques with heightened risks of cardiovascular complications, particularly myocardial infarction and cardiac arrest (12). Patient-controlled intravenous analgesia (PCIA), while demonstrating efficacy in postoperative pain management, presents a distinct adverse effect profile. Opioids administration correlates with nausea/vomiting rates exceeding 50% (13). In contrast, regional nerve blocks with local anesthetics demonstrates dual clinical benefits: a significant reduction in opioid consumption and a lower incidence of systemic adverse events compared to conventional analgesia approaches. However, a critical limitation persists: current local anesthetics fail to provide analgesia of sufficient duration, which fundamentally restricts the clinical applicability of single-injection regional nerve blocks for postoperative pain management, despite their proven intraoperative performance.

Liposomal bupivacaine, an innovative sustained-release local anesthetic with a favorable safety profile (14), utilizes multivesicular liposomal technology to encapsulate bupivacaine within phospholipid vesicles. This structural characteristic enables gradual drug release, achieving extended analgesic duration while maintaining therapeutic concentrations (15). Additionally, existing evidence indicates that bilateral quadratus lumborum (QL) blocks provide more effective postoperative pain relief than transversus abdominis plane (TAP) blocks—well-established regional anesthesia technique (16–18). Given the prolonged analgesic duration of liposomal bupivacaine and the superior efficacy of QL blocks, this study aims to evaluate the efficacy of bilateral quadratus lumborum block with liposomal bupivacaine for post-cesarean analgesia.

## Methods

2

This protocol adheres to the Standard Protocol Items: Recommendations for Interventional Trials (SPIRIT) guidelines.

### Study design and patients

2.1

This study is a single-center, prospective, randomized, open-label, parallel-group clinical trial. The trial will be conducted at the Affiliated Hospital of Qingdao University, enrolling a total of 201 patients. Recruitment is scheduled to take place from 20th January 2025 to 10th December 2025. The study flow diagram is shown in Figure 1.

**Figure 1 fig1:**
[figure not shown]
Study flow diagram. Grouping according to modes of Intervention. LB, liposomal bupivacaine; R, ropivacaine; P, patient-controlled intravenous analgesia pump.

### Inclusion criteria

2.2

Patients who meet the following criteria will be included.

Aged 18 and above;Singleton pregnancy;Scheduled for elective cesarean section;Individuals who provide consent to participate in this study and sign the informed consent document.

### Exclusion criteria

2.3

The exclusion criteria include.

Contraindication to spinal or regional anaesthesia;Known hypersensitivity to trial-related medications;Significant cardiovascular or pulmonary disease;Suffered from severe liver or kidney dysfunction;Having a history of significant mental or other health conditions, or an inability to communicate, which precludes assessment or examination;Past medical history of neurological deficits;Chronic pain conditions or current use or abuse of opioids or alcohol.

### Primary outcome

2.4

The primary outcome is postoperative pain intensity, assessed using the Visual Analogue Scale (VAS) during standardized movement (instructing patients to turn over) at 12, 24, 48, and 72 h post-surgery. The VAS pain score ranges from 0 (indicating no pain) to 10 (indicating intolerable pain) points. In this longitudinal analysis, a generalized estimating equation (GEE) model with exchangeable correlation structure will be employed to evaluate overall differences in pain scores among groups across the four predefined postoperative intervals.

### Secondary outcomes

2.5

Secondary outcomes will include patient self-assessment of the Quality of Recovery-15 (QoR-15) scale at 24 and 48 h postoperatively, as well as Visual Analog Scale (VAS) pain scores at rest, recorded at 12, 24, 48, and 72 h post-surgery. Additionally, the number of postoperative acute analgesic requests will be documented. Postoperative anxiety regarding the hypothetical repeat cesarean section will be assessed at 72 h post-surgery using the VAS score (scores range from 0 to 10, with 0 indicating the best and 10 indicating the worst, named VAS anxiety score) (19). Subjective sleep quality will be evaluated for 24, 48, and 72 h post-surgery using the Numerical Rating Scale (NRS) (scores range from 0 to 10, with 0 indicating the worst and 10 indicating the best sleep quality). The maximum walking duration, defined as the longest duration a patient can walk after surgery, will be measured at 24, 48, and 72 h post-surgery. Patient satisfaction with analgesic management will be assessed at 24, 48, and 72 h post-surgery using the NRS (scores range from 0 to 10, with 0 indicating the worst and 10 indicating the best). Postoperative opioid use (including sufentanil via PCIA and any rescue oxycodone) will be recorded over the 0–72 h period. For comparability, all opioid doses will be converted to intravenous morphine milligram equivalents (MME) using standard equianalgesic conversion factors. Both the raw consumption of sufentanil and oxycodone as well as the total MME will be reported. Furthermore, the incidence of nausea and vomiting and length of hospital stay will be recorded.

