### Anaesthetic and study interventions

2.8

All patients fast for at least 8 h and abstain from water for 4 h preoperatively. In the operating room, after establishing a peripheral intravenous channel, they inhale oxygen at 5 L/min via mask, with continuous monitoring of vital signs: non-invasive blood pressure, percutaneous arterial oxygen saturation (SpO_2_), heart rate, and respiratory rate. Preoperatively, all parturients will receive combined spinal-epidural anesthesia. The parturient will be placed in the lateral decubitus position. Following standard aseptic skin preparation and draping with a sterile aperture sheet, subarachnoid blockade will be performed. At the L2/3 or L3/4 interspace, 10–14 mg of 0.5% ropivacaine will be administered intrathecally to achieve rapid onset of surgical anesthesia. An epidural catheter will then be inserted for subsequent intraoperative supplementation if required. In case of inadequate block height or duration, incremental boluses of 2% lidocaine (3-5 mL) or 1% ropivacaine (5 mL) will be administered through the epidural catheter, with careful titration based on the patient’s response and hemodynamic status. Continuous monitoring will be maintained for signs of local anesthetic systemic toxicity, such as tinnitus, perioral numbness, or altered mental status. For parturients with extreme body habitus or height (affecting drug distribution and blockade levels), local anesthetic dosing will be precisely calibrated based on individual anthropometric measurements to optimize analgesic efficacy and safety. Dosing will be precisely calibrated in accordance with each patient’s anthropomorphic measurements to ensure optimal analgesic outcomes. Upon verification of both the requisite analgesic level (at least T6) and the efficacy of the blockade, the cesarean section will be initiated. Supine hypotensive syndrome and total spinal anesthesia are medical emergencies requiring immediate treatment, so, intensive monitoring during the surgical procedure and maintaining hemodynamic stability with the utilization of vasoactive medications as needed to support vital sign parameters are essential. All patients will receive postoperative analgesic regimens as dictated by the sealed-envelope protocol. This information is exclusively known to the anesthesiologist administering the anesthesia, with all other individuals involved remaining blinded to the details. Participants in group LB will receive bilateral QL nerve block [posterior QL block (20)] utilizing liposomal bupivacaine injection under ultrasound guidance (Liposomal bupivacaine injection, 133 mg per 20 mL on each side); participants enrolled in group R-P will receive bilateral QL nerve block utilizing ropivacaine injection under ultrasound guidance (Ropivacaine injection, 20 mL of 0.375% ropivacaine on each side), in conjunction with a PCIA; and participants enrolled in group P will be managed with standard PCIA, without supplementary nerve block interventions. In the preparation of PCIA pumps, each total volume is standardized at 100 mL, and the formulation includes sufentanil and 8 mg of ondansetron. The total amount of sufentanil is calculated based on a dosage of 2 μg per kilogram of body weight. The background infusion rate is set within the range of 0.04 μg/kg/h. The PCIA protocol is set with a 0.04 μg/kg bolus dose and a 15-min lockout interval to ensure safety.

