### Data collection and monitoring

2.9

Data collection will encompass a range of patient characteristics, including age, height, weight, body mass index (BMI), ASA score, drinking status, smoking status, parity, duration of surgery, intraoperative bleeding, and intraoperative analgesia grade. All pertinent data will be meticulously recorded in case report forms (CRFs) and subsequently inputted into an electronic database under the vigilant supervision of the principal investigator (Table 1). An independent Data Monitoring Committee (DMC) will be tasked with the ongoing oversight of the data collection process. Upon completion of data registration, the electronic database will be safeguarded. De-identified datasets will then be forwarded to an independent statistician for comprehensive analysis in accordance with a predefined statistical plan. Any serious adverse events (SAEs), whether or not they are related to the study medication (e.g., persistent hemodynamic instability), must be promptly reported to the principal investigator. In such instances, the perioperative care team is obligated to implement necessary measures to safeguard participant wellbeing. Furthermore, these SAEs must be communicated to the DMC within a 24-h window for thorough discussion and to determine if any adjustments to the study interventions or the study’s discontinuation are warranted.

**Table 1 tab1:** Schedule of patient enrolment, study interventions and outcome assessment.

	Study period							
	Enrollment	Allocation	Post-allocation					Close-out
Time point	Pre-op visit	Pre-op 1 day	0 h post-op	12 h post-op	24 h post-op	48 h post-op	72 h post-op	Discharged
Patient enrolment								
Eligibility criteria	×							
Written informed	×							
Consent								
Demographic data	×							
Baseline characteristics	×							
Randomization/allocation		×						
Study interventions								
Liposomal bupivacaine			×					
Ropivacaine & PCIA			×					
PCIA			×					
Outcome assessment								
VAS pain score during turning over				×	×	×	×	
VAS pain score at rest				×	×	×	×	
QoR-15 scale					×	×		
Need for rescue analgesia				×	×	×	×	
VAS anxiety score							×	
NRS sleep score					×	×	×	
Maximum walking duration					×	×	×	
NRS for satisfaction with analgesic					×	×	×	
Opioid consumption								×
Length of hospital stay								×
Nausea			×	×	×	×	×	
Vomiting			×	×	×	×	×	
Adverse events								
Allergy			×	×	×	×	×	
Wound infection			×	×	×	×	×	
Lightheadedness			×	×	×	×	×	
Headache			×	×	×	×	×	

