### Statistical analysis

2.11

The normality of continuous variables will be assessed using the Shapiro–Wilk test. Data following a normal distribution will be reported as mean (standard deviation, SD), while non-normally distributed data will be presented as median (interquartile range, IQR). Binomial variables will be expressed as proportions. A generalized estimating equation (GEE) model will be used to analyze repeated measures of continuous variables, including VAS scores, QoR-15 scores, maximum walking duration, and subjective sleep quality, accounting for within-subject correlations. The correlation structure will be selected based on the quasi-likelihood under the independence model criterion (QIC). Data distribution will determine the use of either a normal or gamma distribution with identity or log-link functions. *Post hoc* pairwise comparisons will be Bonferroni-corrected. Continuous variables measured at a single time point, such as hospital stay and sufentanil consumption, will be analyzed using *t*-tests or Mann–Whitney U tests depending on normality. Categorical data will be analyzed using the *χ*^2^ test, with *p*-values adjusted using the Bonferroni method and set at 0.017 for pairwise comparisons. Statistical significance will be defined as *p* < 0.05.

All study outcomes will be analysed in the modified intentiontotreat population, including all patients who undergo randomisation with relevant data available. Patients will be included in the analysis according to their original allocation. Multiple testing corrections for secondary outcomes will not be applied; therefore, these outcomes should be interpreted as exploratory findings. Odds ratios (OR) and corresponding 95% confidence intervals (CI) will be reported where appropriate. No interim analysis will be planned. Missing data will not be imputed. Statistical analyses will be performed using SPSS (version 25.0; IBM SPSS). A two-sided *p*-value < 0.05 will indicate statistical significance, except where false discovery rate (FDR) corrections apply.

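### Sufentanil is dosed per kilogram but compared as an unadjusted raw total, so body weight adds avoidable noise to R-P v P; once a single fill is empty, only bolus counts would show demand

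*Protocol article*

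**What the plan says.** Three parts of the protocol article bear on this point.

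- **Dosing (2.8, Anaesthetic and study interventions).** For the pump fill: "The total amount of sufentanil is calculated based on a dosage of 2 μg per kilogram of body weight". For the infusion: "The background infusion rate is set within the range of 0.04 μg/kg/h". The bolus is 0.04 μg/kg. The 15-minute lockout, the 100 mL volume and the 8 mg of ondansetron do not depend on weight. Groups R-P and P have a pump; group LB does not.
- **Outcome (2.5, Secondary outcomes).** Opioid use "will be recorded over the 0–72 h period", and "Both the raw consumption of sufentanil and oxycodone as well as the total MME will be reported". No per-kilogram measure is defined.
- **Analysis (2.11, Statistical analysis).** Single-time-point variables, "such as hospital stay and sufentanil consumption, will be analyzed using *t*-tests or Mann–Whitney U tests depending on normality". No unit and no covariate is given. Secondary outcomes are labelled exploratory and carry no multiplicity correction.

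Weight is among the characteristics listed in 2.9: "age, height, weight, body mass index (BMI), ASA score, drinking status, smoking status, parity". Pump bolus counts are not on that list, and Table 1 shows opioid consumption only at discharge.

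**The concern.** While the pump runs, the sufentanil delivered is body weight multiplied by a per-kilogram amount. In that amount, only the number of boluses reflects what the patient asked for; the background is fixed by the settings. Two women with identical demand but different weights therefore have different raw totals. MME is a linear conversion of the sufentanil dose plus any oxycodone, so its sufentanil part carries the same weight effect.

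An unadjusted two-sample test leaves this variation in the error term. R-P v P is where it matters. LB has no pump, so its PCIA sufentanil is zero by design, and any contrast with LB largely reflects that design. R-P v P is the only pair in which sufentanil use can show how a block changes demand on the pump. The Discussion and Conclusion present opioid sparing as one of the trial's interests, so a less precise answer has some cost.

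**Working it through.** The article states no variance, effect size or power for sufentanil, so there is no figure of its own to reproduce.

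**1. Model.** Let W be weight, H the hours the pump runs and K the boluses delivered. The background is taken as fixed at 0.04 μg/kg/h, the only value given.

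- Per-kilogram dose: D = 0.04 × (H + K).
- Raw dose: T = W × D.

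**2. Weight's share of the raw variance.** With W and D independent, the squared correlation of W with T is

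share = CV_W² / (CV_W² + CV_D² + CV_W² × CV_D²), where CV_D = SD(K) / (H + mean K).

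The following inputs are assumptions, not figures from the article: mean weight 75 kg; weight CV 12, 15 or 18%; mean boluses 5 to 40.

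Worked example, 72 h, K mean 15 and SD 12, weight CV 15%: CV_D = 12/87 = 0.138, so share = 0.0225 / (0.0225 + 0.0190 + 0.0004) = 0.54. Simulation with 200,000 draws gives the same 54%.

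Simulated shares with the pump kept supplied, at weight CV 12/15/18%:

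| Mean boluses (SD) | 72 h | 48 h |
|---|---|---|
| 5 (5) | 77/84/88% | 61/71/77% |
| 10 (8) | 60/70/76% | 43/54/62% |
| 15 (12) | 43/54/62% | 28/37/46% |
| 20 (15) | 35/45/53% | 23/31/39% |
| 30 (25) | 19/27/34% | 12/18/23% |
| 40 (35) | 13/18/24% | 8/12/16% |

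**3. Power, R-P v P.** 67 per arm (2.7), two-sided 0.05 (2.11), weight CV 15%, bolus SD 0.8 × mean, over-dispersed counts, t-test, 4,000 simulated trials per row, pump kept supplied:

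| Mean boluses, P v R-P | 72 h: raw → per kg | 48 h: raw → per kg |
|---|---|---|
| 15 v 10 | 43% → 84% | 56% → 82% |
| 20 v 12 | 70% → 95% | 82% → 96% |
| 20 v 15 | 30% → 53% | 39% → 54% |
| 30 v 20 | 64% → 83% | 72% → 83% |

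**4. The fill against the window.**

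- Background over 72 h: 0.04 × 72 = 2.88 μg/kg, more than the 2 μg/kg fill.
- Time to empty with no bolus: 2 / 0.04 = 50 h.
- By 48 h the background has used 0.04 × 48 = 1.92 μg/kg, which leaves (2 − 1.92) / 0.04 = 2 boluses.

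If one fill is used and not replaced, raw use tends to 2 μg/kg × weight. Weight's share is then 99–100% in the simulations for 48 h and 72 h. Dividing by weight gives about 2 μg/kg for nearly everyone. Simulated power in the scenarios of step 3 is 0–11% per kilogram, against about 5% raw. Here the ceiling hides demand, and a per-kilogram total does not bring it back.

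**The case against.** The strongest case on the other side has five parts.

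- **The unit is inferred.** In 2.5, raw is set against the MME conversion, and 2.11 names no unit. Section 2.9 refers to a predefined statistical plan that is not shown and might settle this. That is fair. Still, raw consumption and MME are the only sufentanil measures the article defines, and the test it names is unadjusted.
- **Only precision is lost, in an exploratory outcome.** This stands in full. A reader might infer that an imbalance in mean weight biases the comparison. It does not: randomisation balances weight on average, chance imbalance is already counted in the standard error, and the test keeps its type I error.
- **R-P v P is not a key contrast.** The Discussion names LB v P and LB v R-P. This stands and lowers the priority. It does not make the noise useful in the pair where it occurs.
- **The size depends on unknown inputs.** A reader might infer that weight supplies at least half of the variance, or that power is roughly halved. The article supports neither as a general statement. Shares fall to about 10% when demand is high and variable. The 72 h scenarios also need more drug than one fill holds: 20 boluses would take 0.04 × 92 = 3.68 μg/kg, and no refill is described.
- **Demand is measured elsewhere.** Acute analgesic requests and rescue need at four times capture part of it, but not pump demand.

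**Conclusion.** The point holds as a low-cost gain in precision. All sufentanil dose settings scale with weight, the defined measures do not allow for it, and the named test does not adjust. The lost precision affects R-P v P only.

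Its size cannot be fixed from the article. Weight's share of raw variance runs from about 10% (many, variable boluses) to nearly 100% (a single fill emptied), depending on weight spread, bolus counts and refill practice, none of which is given. With the pump kept supplied, the per-kilogram analysis had more power in all eight scenarios, with gains from 11 points (72% to 83%) to 41 points (43% to 84%). With a single unreplaced fill the per-kilogram total is also uninformative, and delivered boluses are the measure to use.

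**What to change.** 1. In 2.5 and 2.11, state that sufentanil for R-P v P is analysed in μg/kg, or as the raw dose with body weight as a covariate. Keep raw μg as a descriptive figure.
2. Adjust total MME for weight in R-P v P only. A common weight term across all arms would not fit: LB has no weight-based opioid, and rescue oxycodone starts at a flat 5 mg.
3. Analyse the number of delivered boluses, taken from the pump record, as a measure in its own right.
4. Reconcile the 2 μg/kg fill, the 0.04 μg/kg/h background and the 0–72 h recording window, and state what happens to the pump and to the outcome once the fill is empty. Which setting is right is for the investigators.

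**Cost.** A few lines of text. Weight is already collected, and the two-sample test can stay for μg/kg. Bolus counts must be added to the recorded data, and a regression replaces the simple test for MME in this pair.
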